### Criteria for discontinuing or modifying allocated interventions {11b}

The study of an individual patient will be terminated by investigator or by the attending physician at any moment during the treatment in the ICU if the safety of the patient cannot be otherwise assured. Thereafter, the patient will be treated by the most appropriate means according to the judgment of the attending physician. Each individual case will be considered by the attending physician according to clinical evidence of intensive care medicine.

The study subjects may be withdrawn from their study treatment prematurely by the investigator or by the physician for one or more of the following reasons:

A failure to maintain a xenon concentration ≥ 30 %A failure of ventilation and/or oxygenation of the patient with the xenon delivery deviceAdverse event (AE)/serious adverse event (SAE)Protocol violationIf for any reason the investigator or the attending physician believes that continued participation in the study is not in the best interests of the patient.

### Strategies to improve adherence to interventions {11c}

None. Due to the nature of the study, the 24-h xenon treatment will be given to the intervention group and MR imaging will be conducted on those patients where the imaging can be safely performed.

### Relevant concomitant care permitted or prohibited during the trial {11d}

Standard of care, no other special provisions.

### Provisions for post-trial care {30}

Standard of care for all. The treatment studied and research-related procedures are free of charge for study participant. Any loss of earnings and travel expenses caused by the examination visits will be reimbursed to a patient/family member/relative according to the actual costs based on supporting documents. If the study subject suffers personal injury as a result of the study treatment or an action taken as a result of the study, one can apply for compensation. Further details are given in the informational documentation handed out to both the patient and next of kin.

## Outcomes {12}

### Primary outcome measure

Global fractional anisotropy of white matter of diffusion tensor imaging (DTI). White matter damage will be less severe in xenon-treated patients, i.e., global fractional anisotropy will be significantly higher in the xenon group than in the control group as assessed with the 1st MRI.

### Secondary outcome measures

Fractional anisotropy of white matter at cerebellum and/or at corpus callosum as assessed with the 1st MRI.Safety and tolerability of xenon, as assessed with a ratio of adverse events, serious adverse events, and suspected unexpected serious adverse reactions (SUSARSs) during the follow-up at 1 year between the xenon group and the control group.Composite of radiological EBI (within 72 h after the start of SAH symptoms), DCI, cerebral infarction (see definitions in detail under the section of secondary objectives) and poor outcome (good: mRS 0–2; poor: mRS 3–6) at 3-months and at 1 year.Neurogenic stress cardiomyopathy and stunned myocardium (i.e., myocardial injury caused by sympathetic storm and autonomic dysregulation with hs-troponin elevation, left ventricular dysfunction or ECG changes)ICP-level up to 14 days (i.e., as long as clinically relevant) after the onset of aSAH symptomsNeed for ICP therapies up to 14 days (i.e., as long as clinically relevant) after the onset of aSAH symptomsDuration of therapy for ICP control/monitoring up to 14 days (i.e., as long as clinically relevant) after the onset of aSAH symptomsPlasma catecholamine levelsDifference in selected biomarkers (NSE, NF-L, GFAB, S100B, UCH-L1, total-tau TNF-α, interleukins 6 and 10) and difference in metabolomic and lipidomic profiles in the blood and CSF between xenon and control group in predicting risk for EBI, vasospasm, DCI as well as a good neurological outcome at 3 months, 1 year, and at 2 years after the aSAH.Development of prognostication models with a selected combination of brain imaging and biomarkers obtained from various MRI techniques (see details under the section “Data collection and management”), clinical data, and metabolomics (see details under the section “Data collection and management”) by applying artificial intelligence and machine learning for EBI, vasospasm, DCI, and a good neurological outcome at 3 months, 1 year, and at 2 years after the aSAH.Difference in CTA, DSA, and MRI parameters obtained from various MRI techniques (see details under the section “Data collection and management”) between xenon and control group in predicting EBI, vasospasm, DCI, and a good neurological outcome at 3 months, 1 year, and at 2 years after the aSAH.Predictive value of computational fluid dynamics (CFD) (see details under the section “Data collection and management”) to detect the differences in the blood flow behavior in the recruited patients by applying 3D DSA to assess the risk of EBI within the first 72 h after the start of aSAH symptoms, vasospasm (within 21 days after the start of SAH symptoms) and DCI (between day 4 and 6 weeks after the start of SAH symptoms) and a good neurological outcome at 3 months, at 1 year, and at 2 years after the aSAH (mRS 0–2).Difference of metabolomics and lipidomics profiles of plasma and CSF between xenon and control group and in predicting the risk for EBI within the first 72 h after the start of aSAH symptoms, vasospasm (within 21 days after the start of SAH symptoms) and DCI (between day 4 and 6 weeks after the start of SAH symptoms) and a good neurological outcome at 3 months, at 1 year, and at 2 years after the aSAH (mRS 0-2).Difference of activity of microglial cells between the subjects in the xenon and control groups and in predicting the risk for DCI and a good neurological outcome at 3 months, 1 year, and at 2 years after the aSAH.

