## Introduction

### Background and rationale {6a}

Aneurysmal subarachnoid hemorrhage (aSAH) is a neurological emergency which is associated with a high risk of mortality and permanent disability. Subarachnoid hemorrhages account for approximately 5–10% of all strokes; however, the case mortality rate of aSAH at 1 year is considerably higher (50%) when compared to ischemic stroke. Up to 10–15% of patients with aSAH die before reaching the hospital [1–7]. In addition to mortality, aSAH is associated with a substantial impairment in the quality of life, with significant neurological deficits and psychological sequelae. About one in five survivors of aSAH will not regain functional independence and only every fourth regains the same level of functionality as before the aSAH [1–6]. In worldwide estimates, when compared with ischemic strokes, aSAH patients are disproportionately younger, i.e., of working age with the age at insult mostly below 66 years. In Finland, the mean age of the event is as young as 55 years [8]. Subsequently, aSAH is associated with a considerable loss of independent functionality and responsible for the development of dependency early in life. Novel treatments are needed to mitigate the effects of aSAH both in the immediate aftermath (early brain injury, EBI) and thereafter to improve the current dismal outcomes.

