EBI is a major cause of mortality in aSAH patients [9–11]; it is defined as the period within the first 72 h after the ictus and describes the immediate overall brain injury after the aSAH. The initial clinical severity of the aSAH is the most important factor determining the overall outcome; this is assessed by a preliminary assessment of radiographic findings and neurological consciousness using the Glasgow Coma Scale (GCS), together with Hunt-Hess or WFNS grading. Initial radiographic markers of EBI (e.g., cytotoxic edema) are significant predictors of secondary complications and outcomes [9–11]. The pathophysiological disturbances underlying the radiographic findings during the EBI period are not completely understood; however, acute global ischemia, ischemia/reperfusion injury from the transient circulatory arrest at ictus, increased intracranial pressure (ICP), decrease in cerebral blood flow (CBF), and perfusion pressure (CPP) are clinically relevant pathological processes which can result in neuronal death. In addition, other pathophysiological mechanisms during the EBI period include disruptions of the blood-brain barrier, brain swelling, vasogenic and cytotoxic edema, acute vasospasm, dysfunction of autoregulation, altered ionic homeostasis, disruption of vascular integrity, excitotoxicity (e.g., via glutamate-activated receptors), thrombin activation, oxidative stress, inflammation (via activation of microglial cells), increased levels of matrix metalloproteinase (MMP) 9, and activation of the nitric oxide synthase (NOS) pathway. It has been suggested that there may be a causal relationship between delayed cerebral ischemia (DCI) and the severity of EBI. Therefore, an implementation of new treatment modalities targeting EBI seems to represent a promising avenue to attenuate its secondary injuries such as DCI and cerebral infarction [9–11].

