Even after successful microsurgical or endovascular treatment of the ruptured aneurysm, DCI is still a potentially devastating clinical syndrome related to aSAH and it is the most significant cause for morbidity and mortality in patients who survive the initial aSAH [1–3, 12]. DCI is a clinical syndrome of focal neurological and cognitive deficits presenting in about 30% of aSAH patients at 3–14 days after the initial insult, which might progress to infarction [1–5, 12]. While an angiographically evident vasospasm in the cerebral arteries can be detected in 70% of patients, less than half of them develop any symptoms or ischemia in the territory supplied by the narrowed artery [1]. In addition, treatment with the calcium-channel blocker, nimodipine, which is currently the standard of care and the only pharmacological intervention that has been shown to reduce the risk of DCI and improve neurologic outcome by one-third after aSAH, does not alter the incidence or severity of delayed cerebral artery vasospasm [13]. Furthermore, other clinical trials involving drugs that exert a significant impact on vasospasm did not have any impact on the risk of DCI or outcomes [1, 12, 14]. Consequently, recent research has questioned whether there is truly a direct causal relationship between cerebral vasospasm and DCI and it has been suggested that DCI following an aSAH is actually the result of a variety of different pathophysiological mechanisms, which are currently incompletely understood [1, 12, 15, 16]. From preclinical and clinical studies, a number of possible mechanisms other than vasospasm to explain the link between DCI and infarction have been proposed including microthromboembolism, cortical spreading depolarization and ischemia, microcirculatory dysfunction, inflammation, and impaired cerebral autoregulation [12]. It has been recommended that the main outcomes of clinical trials investigating strategies to prevent DCI should measure the extent of cerebral infarction by either radiologic imaging or autopsy biopsy as well as the patient’s functional outcome [17].

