#### Objectives

The primary objective is:

To explore whether xenon is neuroprotective in aSAH patients.

The secondary objectives are to explore the neuroprotective effects of xenon on:

The white matter injury in the cerebellum and corpus callosum. Recent studies have revealed that fractional anisotropy of white matter at 72 h post-SAH measured globally, in the cerebellum and in the corpus callosum, had an independent predictive value for both DCI and for a poor neurological outcome (i.e., mRS 3-6) [44].The incidence and severity of EBI within 72 h after the appearance of SAH symptoms, DCI, and cerebral infarction (according to a consensus statement [17] and consensus guidelines [5]: (1) DCI is defined as a new focal neurological deficit (such as hemiparesis, aphasia, apraxia, hemianopia, or neglect) or a decrease of at least 2 points in the Glasgow Coma Scale (either in the total score or in one of its individual components). This should last for at least 1 h and not be due to other causes (e.g., hydrocephalus, seizures, metabolic derangement, infection, sedation). DCI is not apparent immediately after aneurysm occlusion and cannot be attributed to other causes by means of clinical assessment, CT or MRI scanning of the brain, and appropriate laboratory studies; (2) cerebral infarction is defined as a new infarct on follow-up imaging (i.e., in any of the following: 2nd MRI, CT, CTA, DSA, and perfusion CT) between day 4 and 6 weeks after the initial appearance of SAH symptoms.The incidence of adverse events, serious adverse events, suspected unexpected serious adverse reactionsThe inflammatory process, i.e., assessed by the extent of microglial activation and the levels of cytokine in cerebral spinal fluid (CSF)The need and duration of intracerebral pressure (ICP) treatmentsPlasma catecholamine levelsThe release of troponin TThe release of neuron-specific enolase (NSE), neurofilament light (NF-L), glial fibrillary acidic protein (GFAP), calcium-binding protein S100B (S100B), ubiquitin carboxyterminal hydrolase L1 (UCH-L1), total tau, and cytokines (tumor necrosis factor alpha, interleukins 6 and 10)

The exploratory objectives are:

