To explore the predictive value of the different MRI techniques (see details under the section of “Data collection and management”) alone and combined for clinical outcome at 3 months, and also at 1 and 2 years after SAH.To examine the pathophysiological pathways of the post-SAH period between the two treatment groups and to assess the predictive value of selected proteomics and metabolomics on severity of EBI and DCI and neurological outcome (i.e., good outcome: mRS 0–2 vs poor outcome: 3–6)To evaluate the role of microglial activation (see details under the section of “Data collection and management”) on the development of DCI.To explore the role of the cytokine level on the development of DCITo assess a combination of selected brain imaging markers obtained from different MRI techniques (see details under the section of “Data collection and management”), biomarkers (see secondary objectives # 8), plasma metabolomics (see details under the section of “Data collection and management”), CSF metabolomics and clinical examinations (e.g., motor score, pupillary light reflex with pupillometry, epileptic seizures) as a prognostication model for EBI, DCI, and neurological outcome at 3 months, at 1 and 2 years after SAH (i.e., good outcome: mRS 0–2 vs poor outcome: 3–6).To test the applicability of utilizing a brain network analysis with graph theoretical analysis and anatomical connectivity of white matter tracts (see details under the section of “Data collection and management”) in prognostic models for EBI, DCI, and neurological outcome at 3 months, at 1 and 2 years after SAH (i.e., good outcome: mRS 0–2 vs poor outcome: 3–6) and to investigate xenon’s effect on the connectivity.To unravel the mechanisms underpinning the development of EBI and DCI by utilizing brain imaging obtained from different MRI techniques (see details under the section of “Data collection and management”) and metabolomics (i.e., plasma and spinal fluid; see details under the section of “Data collection and Management”)To measure the clinical neurological outcome at 3 months and at 1 year and at 2 years.To develop a prognostication model for EBI and DCI and neurological outcome at 3 months and at 1 year and at 2 years after SAH

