### Trial design {8}

The Xe-SAH study is a prospective, multicenter phase II drug intervention trial. The study design is a single-blind, prospective superiority randomized two-armed parallel follow-up study. The primary objective of the study is to explore the potential neuroprotective effects of xenon, when administered within 6 h of the initial insult, in adult (≥ 18 years of age), mechanically ventilated aSAH patients with a Hunt-Hess grading of 3–5. There are two study arms: the control arm receiving the current standard of care while the intervention arm will be administered a 24-h xenon treatment in addition to the standard care.

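### DCI and cerebral infarction, a stated secondary objective, and mRS are between-arm outcomes only inside a composite with undefined radiological EBI, which could dilute a clinical effect

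*Protocol article*

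**What the plan says.** **Outcome list.** Under Secondary outcome measures, one item is a "Composite of radiological EBI (within 72 h after the start of SAH symptoms), DCI, cerebral infarction" "and poor outcome (good: mRS 0–2; poor: mRS 3–6) at 3-months and at 1 year". It refers the reader to the secondary objectives for definitions. In the other items, DCI and neurological outcome appear as things to be predicted from biomarkers, imaging, blood-flow modelling or metabolomics. Infarction does not appear again.

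**Objectives.** The secondary objectives are broader. One is xenon's effect on "The incidence and severity of EBI within 72 h after the appearance of SAH symptoms, DCI, and cerebral infarction", written as a list and not as a composite. It defines DCI and cerebral infarction (a new infarct between day 4 and 6 weeks). It gives no criterion for radiological EBI. Functional outcome is only an exploratory objective, "To measure the clinical neurological outcome at 3 months and at 1 year and at 2 years", with no comparison of arms mentioned.

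**What EBI means.** The Background says of EBI that "it is defined as the period within the first 72 h after the ictus and describes the immediate overall brain injury after the aSAH".

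**Population and timing.** The trial enrols "mechanically ventilated aSAH patients with a Hunt-Hess grading of 3–5". Xenon may start up to 6 h after symptom onset.

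**Cited recommendation.** The Background reports that trials of DCI prevention "should measure the extent of cerebral infarction by either radiologic imaging or autopsy biopsy", together with functional outcome.

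**The concern.** Objectives and outcome measures should correspond. Here a secondary objective on DCI and infarction has no outcome measure of its own, and the only outcome that compares the arms on mRS combines it with three other components.

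The composite also has a weak component. EBI is timed from symptom onset, not from randomisation, and the Background speaks of initial radiographic markers of EBI. Changes visible on the admission scan can therefore count as events, although treatment given later cannot prevent them. The promised definition covers DCI and infarction only, so nothing in the article excludes such changes.

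If EBI is frequent in this severe population and its presence is largely fixed before treatment, it will supply most of the events. A difference in DCI or mRS would then be hard to see in the composite, and no other listed outcome would show it.

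**Working it through.** **The plan's own figure.** The only power statement concerns global fractional anisotropy: difference 0.02, SD 0.035, two-sided 0.05, 80% power. n per arm = 2 × (1.960 + 0.842)² × 0.035² / 0.02² ≈ 48.1, so 49 per arm or 98 in total. The stated 100 is reproduced. Nothing is stated for the composite, so what follows is a scenario and not a correction of a published number.

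**Inputs from the article (all-grade aSAH).** One-year mortality is 50%. "About one in five survivors of aSAH will not regain functional independence". Poor outcome is then 0.50 + 0.50 × 0.20 = 0.60. DCI is about 30%. Enrolment is 80 per arm.

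**Assumptions.** A patient has the event if any component occurs. Components are independent. Xenon lowers poor outcome from 60% to 45% and DCI from 30% to 20%. The EBI rate E is unknown and is varied from 50% to 90%. Infarction is left out because the article gives no rate. All 80 per arm are assessed.

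**Event rates**
- DCI or poor outcome, without EBI: control 1 − 0.40 × 0.70 = 0.72; xenon 1 − 0.55 × 0.80 = 0.56.
- With EBI unaffected: control 1 − 0.28(1 − E); xenon 1 − 0.44(1 − E). The difference is 0.16(1 − E), so it shrinks in proportion to the share of patients free of EBI.
- With EBI cut by 25%: xenon 1 − 0.44(1 − 0.75E).

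**Power** (two proportions, two-sided 0.05): Φ{[d − 1.96√(2p̄(1 − p̄)/n)] / √([p₁(1 − p₁) + p₂(1 − p₂)]/n)}, where d is the difference, p̄ the mean of the two rates and n = 80.

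mRS alone: d = 0.15 and p̄ = 0.525, so (0.15 − 1.96 × 0.0790)/0.0781 = −0.06, which gives power 48%.

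| EBI rate | Control | Xenon, EBI unchanged | Difference (points) | Power | Xenon, EBI cut 25% | Power |
|---|---|---|---|---|---|---|
| 50% | 86.0% | 78.0% | 8.0 | 26% | 72.5% | 56% |
| 70% | 91.6% | 86.8% | 4.8 | 16% | 79.1% | 61% |
| 90% | 97.2% | 95.6% | 1.6 | 8% | 85.7% | 74% |

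**Second scenario.** Take a relative risk of 0.70 on both DCI (30% to 21%) and poor outcome (60% to 42%). Power is 26% for DCI alone, 63% for poor outcome alone and 65% for the two combined without EBI. Adding an unaffected EBI component lowers this to 44% at an EBI rate of 30% and to 9% at 90%. If EBI is also cut by 30%, power is 65% to 86%.

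**Dependence between components.** If DCI occurs only in patients with poor outcome, the control rate before EBI is 60% and not 72%. If all components are fully nested and EBI is at least as frequent as poor outcome, an unaffected EBI component removes the difference altogether. If EBI is nested and rarer than poor outcome in both arms, it costs nothing.

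**The case against.** **DCI and infarction are separate in the objectives.** This stands. A reader of the outcome list might infer that the protocol never intends to compare them on their own. The secondary objectives say otherwise, and the statistical section provides odds ratios for categorical outcomes and Cox models for end-point events. The finding is therefore a mismatch between two sections, not a missing intention. For mRS the gap is wider, because its only separate objective is exploratory and names no comparison.

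**The scoring rule and the EBI rate are not in the article.** This also stands. Any-component scoring is the usual meaning of a composite, but it is not stated and may be set elsewhere. A reader might conclude that the composite will be nearly saturated in intubated Hunt-Hess 3–5 patients. That is plausible, but no rate or threshold supports it. The all-grade inputs could be wrong in either direction: severe grades raise the rates, while the mortality figure may include deaths before hospital, and those patients could not be enrolled.

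**Xenon is meant to act on EBI.** This is the strongest argument. If it does so by about 25%, the composite does better than mRS alone (56–74% against 48%). The loss appears only when the effect on EBI is small. Two points limit the argument: EBI already present at admission cannot be prevented, and a yes/no component does not register reduced severity.

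**Separate outcomes are underpowered too.** True. Separation gives interpretable estimates, not confirmation.

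**The cited recommendation is not breached.** Agreed. Infarction and functional outcome are both measured.

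**Conclusion.** The point holds as an inconsistency between objectives and outcomes, with a definition that the cross-reference does not supply. Both are visible in the text and need no assumption.

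The dilution is conditional. Under the stated scenario, composite power is 26% to 8% for EBI rates of 50% to 90% if xenon leaves EBI unchanged, against 48% for mRS alone. With a cut in EBI of about 25% there is no loss. The documents do not support saying that a real benefit would be hidden. They support saying that it could be, if EBI is common and largely unaffected by treatment. The primary outcome and its sample size are not touched.

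**What to change.** - List as separate secondary outcomes: DCI; cerebral infarction (day 4 to 6 weeks); and mRS 3–6 at 3 months and at 1 year. Give each an arm difference with a 95% CI, and describe them as estimates and not as confirmatory tests.
- Keep the composite as a supportive outcome and report each component beside it by arm.
- Supply the missing criterion for radiological EBI and, within the composite, count only EBI that is new relative to the admission imaging.

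The cost is wording in the outcome section, since these data are already to be collected. The downside is a few more secondary comparisons, each with limited power at 80 per arm.

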## Data collection and management

### Plans for assessment and collection of outcomes {18a}

Upon hospital arrival and thereafter, basic patient information will be recorded in an electronic web-based study database (RedCap). The data collected on aSAH patients is intended to be both quantitative and qualitative in nature, as recommended by the recent recommendations issued by the working group on subjects’ characteristics, including all relevant Common Data Elements (CDE) [47, 48]. The data to be collected will include details of the patient’s age, sex, home medications and health status, time of insult, hospital arrival delay, vital signs, and blood tests. First computed tomography (CT), computed tomography angiography (CTA), and digital subtraction angiography (DSA) results will be registered in the web-based study’s database according to CDE specifications. During the ICU stay, surgical interventions, vital signs, changes in clinical status, and other medical treatments received will be recorded. The duration of xenon administration will be recorded. In addition, arterial blood gas samples will be monitored hourly during the xenon-treatment phase, and then at least every 4 h or whenever clinically indicated during the ICU stay. The results of the MRI scans at 72 ± 24 h and 42 ± 4 days after the onset of SAH symptoms will be collected in detail according to the CDE recommendations.

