### Plans for collection, laboratory evaluation, and storage of biological specimens for genetic or molecular analysis in this trial/future use {33}

Biochemical assessment: A blood sample of 20 ml for determination of plasma catecholamines, plasma metabolomics (see details of metabolomics under the section “Data collection and management”), cardiac enzyme release (P-hs-troponin-T and heart fatty-acid binding protein), neuron-specific enolase (NSE), neurofilament light (NF-L), glial fibrillary acidic protein (GFAP), calcium-binding protein S100B (S100B), ubiquitin carboxyterminal hydrolase L1 (UCH-L1), total tau, and cytokines (tumor necrosis factor alpha, interleukins 6 and 10) will be analyzed at ICU arrival and at 24h, at 48h, and at 72h after onset of SAH symptoms; urine catecholamines during first and second 24 h. In addition, a sample of spinal fluid will be collected through EVD at ICU arrival or as soon as it is in place and at 24h, at 48h, and at 72h after onset of SAH symptoms for assessment of metabolomics. P-hsTn-T and P-NSE will be determined by a local university hospital laboratory with standard methods. The samples will be destroyed 10 years after completion of the study. In addition, the patient has a right to require destruction of the samples at any time. In this study, no tissue samples will be collected, and no genetic analysis are conducted.

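### MRI parameters and the 72 h blood/CSF markers are listed as predicting early brain injury, but they are measured late in, at the end of, or after the 72 h that define it

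*Protocol article*

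**What the plan says.** **The outcome.** Background and rationale {6a} says of EBI that "it is defined as the period within the first 72 h after the ictus and describes the immediate overall brain injury after the aSAH". Secondary outcome measures uses the same limit: "Composite of radiological EBI (within 72 h after the start of SAH symptoms" opens the composite item, and the CFD and metabolomics/lipidomics items repeat the 72 h limit.

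**The predictors.** Four secondary outcome items bear on this point:
- CTA, DSA and MRI parameters, compared "between xenon and control group in predicting EBI, vasospasm, DCI, and a good neurological outcome".
- Blood biomarkers and blood/CSF metabolomic and lipidomic profiles, compared between arms "in predicting risk for EBI, vasospasm, DCI as well as a good neurological outcome".
- Plasma and CSF metabolomics and lipidomics again, with the EBI window written out.
- Machine-learning prognostic models that combine MRI-derived markers, clinical data and metabolomics, with EBI among the targets.

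The exploratory objectives also include prognostic models for EBI, one of which combines MRI markers, biomarkers and metabolomics.

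**The schedule.** Plans for assessment and collection of outcomes {18a} gives the imaging times: "The results of the MRI scans at 72 ± 24 h and 42 ± 4 days after the onset of SAH symptoms". The biological specimens section {33} says that the blood markers "will be analyzed at ICU arrival and at 24h, at 48h, and at 72h after onset of SAH symptoms". CSF follows the same times, except that the first sample may wait until the ventricular drain is in place.

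**The other event windows.** Secondary outcome measures gives "vasospasm (within 21 days after the start of SAH symptoms" and, for DCI, day 4 to 6 weeks.

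**The concern.** A predictor has to be measured before the event that it is meant to forecast. A marker measured while the injury develops, or after it is complete, may simply be a consequence of the injury. It can then separate patients with and without EBI well and still be useless for forecasting, because the value does not exist when a forecast is needed.

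The article aims for models of high predictive accuracy for EBI risk. If MRI parameters and 72 h markers enter those models, the reported accuracy will be read as prognostic performance that no clinician could obtain in time. What is at stake is what the secondary and exploratory models may conclude, not the test of xenon on the primary endpoint.

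**Working it through.** The plan gives no figure of its own to reproduce here. The check compares stated times, all counted from symptom onset.

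**Inputs**
- EBI window: 0 to 72 h (Background and rationale; Secondary outcome measures).
- First MRI: 72 ± 24 h. Second MRI: 42 ± 4 days (Plans for assessment and collection of outcomes).
- Blood/CSF: ICU arrival, 24, 48 and 72 h (specimens section).
- Vasospasm: to day 21. DCI: day 4 to 6 weeks, i.e. day 42 (Secondary outcome measures).

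**First MRI against EBI**
- Scan window: 72 − 24 = 48 h to 72 + 24 = 96 h.
- Share of the EBI window already past at the earliest scan: 48/72 = 67%.
- Share of the scan window after EBI has closed: (96 − 72)/(96 − 48) = 24/48 = 50%.

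**Second MRI against EBI**
- 42 − 4 = day 38 to 42 + 4 = day 46, or 912 to 1,104 h. This lies wholly after 72 h.

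**Samples against EBI**

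| Sample | EBI window elapsed | EBI window left |
|---|---|---|
| 24 h | 24/72 = 33% | 48 h |
| 48 h | 48/72 = 67% | 24 h |
| 72 h | 72/72 = 100% | 0 h |

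The 72 h sample leaves nothing to predict. The 24 and 48 h samples leave 48 and 24 h, so they can predict EBI that appears later, provided that only such EBI is counted.

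**Second MRI against the later events**
- Vasospasm: day 38 is 38 − 21 = 17 days after that window closes.
- DCI: days 38 to 42 of the scan window overlap the last days of the DCI window; days 42 to 46 lie after it.

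**What remains for EBI.** Admission clinical data, the first CT/CTA/DSA (and CFD derived from DSA) and the ICU-arrival samples come early enough to be candidate predictors.

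**The case against.** **A landmark rule is detail for the full protocol or analysis plan.** This is fair for the modelling rules as such, and their absence from an article is not the point made here. The conflict is between times that the article itself states: an outcome that ends at 72 h, and scans and a sample at or after the point where little or none of that window is left.

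**The items list sets of predictors against sets of outcomes, and need not mean every pairing.** This stands in part. The imaging item includes CTA and DSA, which can be early. But EBI is named as a target of MRI parameters, and no scheduled MRI is earlier than 48 h.

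**No hospital measurement can precede the start of EBI, because EBI starts at the ictus.** Correct, so that is not the test applied. The question is whether EBI remains to be predicted once the marker is measured. A reader might infer that all samples from 24 h onward fail; the schedule does not support that, because the 24 and 48 h samples still have part of the window ahead of them. An MRI at 48 to 72 h would likewise be usable only for EBI arising after the scan.

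**Stronger readings that the article does not support**
- *That the second MRI will be used to predict vasospasm or DCI.* No section says so. The secondary objectives give it a role in establishing cerebral infarction. The background's 3 to 14 days for DCI is not the trial's prediction window, and the scan overlaps the end of the window that is.
- *That the first MRI both defines and predicts EBI.* The outcome is radiological, so overlap is a risk, but the article does not say which images establish EBI.
- *That the inflation in accuracy can be quantified.* The planned 0.02 (SD 0.035) is a difference between arms. It says nothing about how far a marker shifts with EBI.

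**Conclusion.** The point holds for EBI. With the stated schedule, neither MRI nor the 72 h blood/CSF sample can deliver prediction of an outcome confined to the first 72 h. The first MRI comes when at least 67% of the window has passed, and half of its permitted range is after the window; the second MRI is weeks later; the 72 h sample falls at the closing boundary. The one partial exception, a first MRI before 72 h, would need a landmark at the scan. Accuracy reported from these sources for EBI as a whole would be association.

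The conclusion rests on the article's own definition of EBI and on the visit times that it gives. It does not extend to admission imaging or ICU-arrival samples, nor to the use of the first MRI and the samples for functional outcome at 3 months, 1 year and 2 years. For vasospasm and DCI, a short statement on the order of predictor and event is a precaution; the article does not commit to an improper use there. The primary fractional anisotropy comparison is untouched. This is a change that should be made to secondary and exploratory outcomes, and no numerical size of bias can be derived from the document.

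**What to change.** Amend Secondary outcome measures, and the EBI models in the exploratory objectives, as follows.

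1. Report relations of the first MRI and the 72 h markers with EBI as associations.
2. Build EBI prediction models from admission clinical data, first CT/CTA/DSA (including CFD) and ICU-arrival samples. Alternatively, use the 24 or 48 h samples with a landmark at the sampling time, counting only EBI that arises afterwards.
3. Keep the xenon-versus-control comparisons of markers measured after treatment has begun, but describe them as treatment-effect or association analyses. Restricting everything to pre-treatment data would leave those items with nothing to compare.
4. For vasospasm and DCI, state that a predictor must precede the event. The second MRI is then used only for later outcomes: mRS at 3 months, 1 year and 2 years.

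The cost is wording only: no new visits, samples or patients. The downside is a smaller set of candidate predictors for EBI and the loss, in landmark analyses, of patients whose event comes before the landmark.
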